### Sample size

During the year 2010, a total of 150 patients were admitted to the obstetrical ward of the Máxima Medical Center for threatening preterm labor which met the inclusion criteria. Approximately 40% of these patients delivered within 7 days. A sample size can be calculated based on an observed difference in test characteristics between the standard diagnostics and the EHG analysis using a fixed allocation ratio of 40 – 60% for the positive and negative group respectively. In the study by Lucovnik et al. an area under the curve of the receiver operating characteristics (ROC) of 0,96 was observed for the EHG analysis and 0,72 for the Bishop score (the best performing test among the standard diagnostics) [5].

A sample of 7 from the positive group and 11 from the negative group achieve 82% power, assuming an area under the ROC curve of 0,95 for EHG CV analysis and 0,70 for the standard diagnostics and using a two-sided *z*-test at a significance level of 0.05. This means a minimal number of 20 patients will need to be included. However, this observed difference is based on a single study. In order to increase the likelihood of detecting a difference in case of a lower observed difference or different allocation ratio, we propose to include a total of 100 patients.

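### The 82% power stated for 7 + 11 women, and the minimum of 20, need an unstated favourable convention or a very high correlation; an actual z-test has about 40–65% power

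*Protocol article*

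**What the plan says.** All of this stands in the Sample size section of the protocol article. The planning assumption is worded "assuming an area under the ROC curve of 0,95 for EHG CV analysis and 0,70 for the standard diagnostics", "using a two-sided *z*-test at a significance level of 0.05", and "using a fixed allocation ratio of 40 – 60% for the positive and negative group respectively". The result is given as "A sample of 7 from the positive group and 11 from the negative group achieve 82% power", followed by "This means a minimal number of 20 patients will need to be included". The section then qualifies itself ("However, this observed difference is based on a single study") and sets the enrolment target with a reason of its own: "In order to increase the likelihood of detecting a difference in case of a lower observed difference or different allocation ratio, we propose to include" 100 patients. It names no correlation between the two tests, no variance model and no convention for the variance under the null.

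**The concern.** Eighteen women is a very small sample for comparing two ROC areas. With 7 positive cases, the AUC of the weaker test (0.70) has a standard error of about 0.13, so a difference of 0.25 is not clearly larger than its own sampling error unless the two estimates are strongly correlated. A power of 82% therefore looks too high. If it is, a published minimum of 20 could be taken up as a planning figure for similar studies of the electrohysterogram, and readers of this study would misjudge how much room the 100 women leave for a smaller advantage.

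**Working it through.** **Inputs (Sample size section).** 7 positive and 11 negative women; AUC 0.95 v 0.70, difference 0.25; two-sided z-test, alpha 0.05 (critical value 1.96); allocation 40:60. The correlation r between the two estimated AUCs is not given, so it is varied.

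**Variance of one AUC (Hanley–McNeil).** Var(A) = [A(1−A) + (n₁−1)(a−A²) + (n₀−1)(b−A²)] / (n₁n₀), with a = A/(2−A) and b = 2A²/(1+A).

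- A = 0.95: [0.0475 + 6 × 0.00226 + 10 × 0.02314] / 77 = 0.00380, SE 0.062.
- A = 0.70: [0.2100 + 6 × 0.04846 + 10 × 0.08647] / 77 = 0.01773, SE 0.133.

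**General power formula.** Power = Φ((0.25 − 1.96√V₀) / √V_A). V_A is the variance of the difference under the assumed AUCs, V_A = v₁ + v₂ − 2r√(v₁v₂). V₀ is the variance used to set the critical value.

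**Reproducing the 82%.** Set V₀ as if both tests had AUC 0.95, so V₀ = 2 × 0.00380 × (1−r).

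- Hanley–McNeil, r = 0.4: √V₀ = 0.0675 and √V_A = 0.1223, so (0.25 − 0.1323)/0.1223 = 0.96 and power is 83%. At r = 0.35 it is 81%.
- Full binormal variance, r = 0: 82.7%.
- Binormal variance without the covariance of the two binormal parameters, score correlation 0.6: 83.3%.

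The other route keeps V₀ = V_A and raises the correlation. At r = 0.85, √V_A = 0.0871, 0.25/0.0871 − 1.96 = 0.91, and power is 82%.

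**Power with the variance the test uses (V₀ = V_A, Hanley–McNeil).**

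| r | SE of difference | Power, 7 + 11 | Power, 8 + 12 |
|---|---|---|---|
| 0 | 0.147 | 40% | 44% |
| 0.3 | 0.129 | 49% | 54% |
| 0.5 | 0.115 | 58% | 64% |
| 0.6 | 0.108 | 64% | 69% |

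The 8 + 12 column is the rounded minimum of 20. For 7 + 11, the full binormal variance gives 48% at 0 and 65% at a score correlation of 0.6, or 69% if 0.6 is taken as the correlation of the AUCs themselves.

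**Simulation.** Equal-variance binormal markers and a paired DeLong z-test at 7 + 11 give about 39%, 43%, 47%, 51%, 61% and 64% power for marker correlations of 0, 0.3, 0.5, 0.6, 0.8 and 0.9 (good to about one point). At a marker correlation of 0.9, the correlation of the two AUCs is only about 0.65, so the 0.85 needed above is out of reach across this range.

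**Why the favourable V₀ does not describe a 5% test.** It applies the precision of the stronger test to both. If both tests shared an AUC of 0.825 (SE 0.110 at 7 + 11), that critical limit would reject with probability 2[1 − Φ(1.96 × 0.0616/0.1097)] = 27%. At a shared AUC of 0.70 it would reject in 36%. These rates do not depend on r.

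**Women needed at 40:60 (V₀ = V_A, Hanley–McNeil, whole numbers per group).** For 80% power: 47, 37, 29 and 27 at r = 0, 0.3, 0.5 and 0.6. For 82%: 49, 39, 32 and 27. Across the variance models, 80% power takes 39–49 at r = 0 and 24–27 at r = 0.6.

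**What 100 women (40 + 60) deliver.** For 0.95 v 0.70, power is 98.6% at r = 0 by Hanley–McNeil, at least 98% in every model with V₀ = V_A, and higher with positive correlation. Against 0.70, 80% power is reached at an EHG AUC of about 0.89, 0.865 or 0.845 for r = 0, 0.3 or 0.5. For an EHG AUC of 0.80, power is 28%, 38% and 49%.

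**The case against.** The strongest reply is that the figure is not a miscalculation. Planning formulas commonly use one variance for the critical value and another for power, and with the null variance at AUC 0.95 the stated 82% returns within two points under several models. That stands: a reader who infers an arithmetic slip goes beyond what the section supports. It also stands that 40–65% depends on the chosen variance model and on a range of correlations that the document does not give; the most favourable combination above reaches 69%. What does not follow is that the 18-woman design has 82% power. The reproducing convention implies a test whose false-positive rate is far above 5% unless both AUCs are near 0.95, and the simulated test does not approach 82%.

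A second reply is that a journal article may leave the correlation and the variance model to the full protocol. That is fair, and their absence alone would be no finding. The point concerns a figure the article does print, which fails over the plausible range of what it leaves out.

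A third reply is that 20 is not the target. That also stands. A reader might infer that the basis for 100 is wrong, or that the plan claims a five-fold margin. The section says neither: 100 is not calculated from 20, no multiple is given, and the text says openly that the planning difference comes from one study. Likewise, the step from observed AUCs of 0.96 and 0.72 to assumed ones of 0.95 and 0.70, and the use of the Bishop score as the best conventional test, are both printed openly and add nothing here.

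**Conclusion.** The concern holds for the 82% and for the minimum of 20, and no further. At 7 + 11 women, a two-sided z-test of 0.95 v 0.70 has about 40–65% power for correlations of 0 to 0.6, and a simulated paired DeLong test has 39–64% for marker correlations of 0 to 0.9. By Hanley–McNeil, 80% power takes about 27–47 women, not 20. The result rests on the stated AUCs and allocation, on variance models that agree closely with each other and with simulation, and on correlations assumed here. Only an AUC correlation near 0.85, or a null variance borrowed from the better test, restores 82%.

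The planned 100 is adequate for the assumed difference. Relative to the recomputed minimum it is a margin of about two-fold (100/47 = 2.1) to nearly four-fold (100/27 = 3.7). What the section lacks is a statement of how small a difference this margin covers.

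**What to change.** In the Sample size section, replace the 82%/20-patient statement with the recomputed power and minimum, naming the assumed correlation and the variance convention. For example: with Hanley–McNeil variances and the same variance for critical value and power, 7 + 11 women give 40% power at r = 0 and 64% at r = 0.6, and 80% power takes about 47 and 27 women respectively. Keep the target of 100 and support it by what it delivers at 40:60: at least 98% power for 0.95 v 0.70, and 80% power for an EHG AUC of about 0.89, 0.865 or 0.845 against 0.70 at r = 0, 0.3 or 0.5.

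The cost is one rewritten paragraph and a less favourable printed figure. Enrolment, procedures and analysis are unchanged.

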### Statistical analysis

Baseline characteristics will be determined for the labor and non-labor group. Differences will be tested for statistical significance using a fisher exact test for dichotomized variables and a non-paired *t*-test for continuous variables. We will evaluate the influence of significant differences in background variables on the outcome using a multivariate logistical regression model.

The Shapiro–Wilk test will be applied to test for a normal distribution of the estimated values of the CV vector amplitude. Levene’s test will be applied to test for equal variances in the labor and non-labor group. An independent samples t-test will be used to test for a significant difference in amplitude of the CV between both groups. The alpha will be set to 0.05 for all statistical tests. Using contingency tables, the sensitivity and specificity of the EHG and standard diagnostics will be determined.

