## Methods and design

### Study population

The population will consist of patients admitted to the obstetrical ward of the Máxima Medical Center Veldhoven and the Jeroen Bosch hospital for threatening preterm labor or preterm prelabor rupture of membranes and who are eligible for treatment with tocolytics and corticosteroids. The decision on treatment will be based on the standard diagnostic tests and local protocol. Administration of tocolytics will be registered: type and dosage, time of administration.

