## Discussion

The study aims to evaluate CV analysis of the EHG as clinical tool for the diagnosis of imminent preterm delivery. In an observational cohort study the EHG will be recorded in patients admitted for threatened preterm labor. The CV will be estimated in the EHG using a fully automated analysis. This automated approach entails a novel automatic selection of contractions based on the eIUP and automatic delay estimation. The diagnostic accuracy will be expressed in terms of sensitivity, specificity and area under the ROC curve for delivery within 1,2,7, and 14 days from the measurement.

Similar to [5], part of the patients will already be treated with tocolytics at the time of the measurement. This could influence the amount of contractions and possibly the CV as well. Using logistic regression, the administration of tocolytics will be tested as possible confounding factor. The EHG CV analysis will be evaluated as diagnostic tool for predicting imminent spontaneous preterm delivery. Although it is not a common scenario in patients admitted for threatened preterm labor, patients within the labor group in which labor is induced will not be included in the final analysis.

Perhaps the biggest challenge and also an essential step in accurate estimation of the CV is recognizing contractions amongst noise and artifacts in the EHG. Different from term patients in labor, preterm patients admitted for threatened preterm labor have mostly an irregular pattern of uterine contractions of a varying frequency as well as duration. Therefore, the detection algorithm cannot assume a regular pattern and fixed duration. Furthermore an external tocodynamometer can fail to show contractions in some patients [40,41]. Therefore, for use as independent clinical tool, the EHG CV analysis cannot rely on the external tocodynamometer as reference. Hence the analysis will be mainly based on the electrical signal recorded on the skin.

Our methods will entail filtering in a narrow frequency band (0,3 – 0,8 Hz) in order to suppress signals other than uterine activity, including (abdominal) striated muscle activity and the maternal electrocardiogram. The eIUP will be used in order to distinguish uterine activity from the background noise. Visual review of the data is envisaged to evaluate the performance of the automatic algorithm.

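### Background covariates are chosen by significance of their baseline difference, and whether tocolytics stay in the logistic model is left open; both should be a fixed set, kept whatever the p-values

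*Protocol article*

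**What the plan says.** The Statistical analysis section compares baseline characteristics between the labor and non-labor groups: "Differences will be tested for statistical significance using a fisher exact test for dichotomized variables", and an unpaired t-test for continuous variables. It continues: "We will evaluate the influence of significant differences in background variables on the outcome using a multivariate logistical regression model". The level is fixed in the same section: "The alpha will be set to 0.05 for all statistical tests". Taken together, this is a selection rule: a background variable is carried into the regression when its baseline difference is significant.

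Tocolytics are handled elsewhere. The Discussion notes that some women will already be treated when the EHG is recorded, says of this that "This could influence the amount of contractions and possibly the CV as well", and then states: "Using logistic regression, the administration of tocolytics will be tested as possible confounding factor". That sentence requires no significant baseline difference. It also does not say what follows from the test. The Study population section shows that the data will exist: "Administration of tocolytics will be registered: type and dosage, time of administration".

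The group comparison of CV amplitude is an unadjusted independent-samples t-test. The accuracy measures are sensitivity, specificity and the area under the ROC curve. The Study parameters/Endpoints section applies the labor/non-labor split at 1, 2, 7 and 14 days.

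**The concern.** In an observational cohort, a p-value for a baseline difference reflects the sample size and the marginal imbalance. It does not show whether the variable distorts the relation between CV and delivery. Three things can follow.

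- A real confounder with a small or moderate imbalance is left out.
- A variable that differs only by chance is let in.
- Because the groups are redefined at each cut-off, the covariate set can differ at 1, 2, 7 and 14 days, so the adjusted results are not comparable.

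A further case matters. A variable that lowers CV but marks women at higher risk of early delivery can look balanced between the groups, because its two effects offset each other. A marginal screen is weakest there.

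For tocolytics the concern is narrower. If being tested means being kept only when significant, adjustment for the one variable the article singles out depends on a p-value.

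At stake is the adjusted association between CV and delivery, assuming CV is a term in the logistic model, as checking for confounding implies.

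**Working it through.** **Inputs from the protocol article.** Total sample: "we propose to include a total of 100 patients". Split: "Approximately 40% of these patients delivered within 7 days", so 0.40 × 100 = 40 labor and 60 non-labor women at 7 days. Alpha is 0.05, taken as two-sided. Splits at the other cut-offs are not given. The article gives no figure for detecting a confounder; its 82% power concerns a comparison of two AUCs, and nothing here rests on it.

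**Assumptions.** The sizes of imbalance, shown as a range.

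**Step 1. Binary variables, Fisher's test at 40/60.** Exact power = Σᵢ Σⱼ Bin(i; 40, p₁) · Bin(j; 60, p₀) · 1{Fisher p ≤ 0.05}.

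| Labor v non-labor | Odds ratio | Detected | Missed |
|---|---|---|---|
| 60% v 50% | 1.5 | 14.5% | 85.5% |
| 40% v 25% | 2.0 | 31% | 69% |
| 60% v 40% | 2.25 | 46% | 54% |
| 75% v 50% | 3.0 | 69% | 31% |
| 80% v 50% | 4.0 | 86% | 14% |

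Detection reaches 50% at an odds ratio of about 2.4 to 3.2, depending on prevalence in the non-labor group (10% to 70%).

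**Step 2. Continuous variables, t-test at 40/60.** Noncentrality = d × √(40 × 60 / 100) = 4.90d, with 98 degrees of freedom. Power is 16% at d = 0.2, 49% at 0.4, 68% at 0.5 and 97% at 0.8.

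**Step 3. Smaller event groups.** If a shorter cut-off gave 20/80, 75% v 50% would be detected in 52% of samples rather than 69%. At 10/90, 60% v 40% would be detected in 20% rather than 46%. Both splits are assumptions.

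**Step 4. Chance imbalances.** With k independent balanced variables each tested at 5%, the chance of at least one significant result is 1 − 0.95ᵏ. For an assumed k = 8 this is 1 − 0.95⁸ = 34%. Fisher's test is conservative, so for binary variables this is an upper figure.

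**Step 5. Opposing effects.** Simulated trials of N = 100 with about 40% events. All of the following are assumed: a binary variable with 50% prevalence that raises the log-odds of delivery by 0.8 and lowers CV by 0.6 SD, and a true CV log-odds of 0.80 per SD.

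| Rule for the variable | Kept in | Mean CV log-odds | 95% interval coverage | Power for CV |
|---|---|---|---|---|
| Baseline Fisher screen | about 9% | 0.72 | about 92% | 90% |
| Kept if its own logistic p < 0.05 | about 40% | 0.80 | 93% | 92% |
| Always kept | 100% | 0.84 | 95% | 94% |

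The first row is the rule for background variables. The second is one reading of the tocolytics sentence. If the variable lowers CV by 1 SD, coverage falls to 86% under the baseline screen and to 89% under p-value retention. If it lowers CV by 0.3 SD, coverage under the screen is 95% and the harm is small.

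**The case against.** Much of the case on the other side stands.

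**Tocolytics are not under the baseline screen.** A reader might infer that they enter the model only if the groups differ significantly on them. The Discussion does not say so: it names them in advance, so the 9% selection rate does not describe their handling. Other readings of being tested do little harm: a 10% change-in-estimate criterion keeps the variable in 76% of simulated trials, with 95% coverage. What remains is that the sentence does not settle which reading applies, and the p-value reading undercovers.

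**The screen does not miss confounders most of the time in general.** That stronger statement holds only below an odds ratio of roughly 2.4 or a difference of roughly 0.4 SD. Strong imbalances are usually found, and the article gives no imbalance figure.

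**Bias is not inevitable, and it is modest.** It also requires an effect of the variable on CV. In a linear model with non-opposing effects of 1 SD on CV, the average bias left after screening is at most about 0.07 SD. In the 0.6 SD scenario, root-mean-square error was slightly lower under the screen (0.263) than with constant adjustment (0.280), and p-value retention centres on the true 0.80; the loss there is in coverage. The linear-model bound does not cover opposing effects, where a small marginal imbalance can accompany real confounding.

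**The main endpoints are untouched.** A reader might infer that diagnostic accuracy is compromised. It is not: the accuracy of CV as a stand-alone test needs no confounder adjustment, and the t-test is unadjusted.

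**An article may leave the covariate list to a fuller document.** True of the list. The rule by which variables enter, however, is stated here, and it is the rule that is at fault.

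**Conclusion.** The point holds in limited form and is worth correcting. Selecting background variables by baseline significance is written into the plan. At 40/60 it misses small to moderate imbalances about half the time or more: 85.5% missed at 60% v 50%, 54% at 60% v 40%, and 51% at 0.4 SD. It misses clearly fewer at 75% v 50% (31%) and at 0.5 SD (32%). It can also admit chance differences and vary the model by cut-off. For tocolytics the defect is an unstated retention rule; if that rule is a p-value, CV coverage is about 89–93% under assumed opposing effects of 1 SD and 0.6 SD on CV.

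The consequence is confined to the adjusted CV association, which can be biased or carry intervals that are too narrow. The detection rates rest on the 7-day split and on assumed imbalances; the coverage figures rest on assumed effects. Neither set is an estimate of what this cohort will show.

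**What to change.** Drop significance of baseline differences as the selection rule; the baseline table can remain as description. State that the logistic model at the 7-day cut-off contains CV amplitude and a fixed set already collected, all kept whatever their p-values: tocolysis at or before the EHG recording (yes/no), membrane status, gestational age and multiple gestation. Tocolytic timing is registered, and the other items follow from eligibility and the measurement procedure. Treat models at the other cut-offs as supportive where events are few. AUC by tocolysis status at recording is an optional descriptive addition.

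The cost is a change of wording and slightly wider confidence intervals. About 40 events for five terms is 40 / 5 = 8 per term, somewhat fewer once induced women in the labor group are left out as the Discussion plans, so the set should stay this short. No new data or visits are needed.

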**Methods/Design:**

The study design will be an observational cohort study. 100 pregnant women, gestational age between 23 + 5 and 34 weeks, admitted for threatening preterm labor or preterm prelabor rupture of membranes, will be included. The length of the cervical canal will be measured by transvaginal ultrasound. The EHG will be recorded using 4 electrodes in a fixed configuration. Contractions will be detected by analysis of the EHG and using an estimation of the intra uterine pressure. In the selected contractions, the delays between channels will be estimated by cross-correlation, and subsequently, the average EHG conduction velocity will be derived. Patients will be classified as labor group and non-labor group based on the time between measurement and delivery. The average conduction velocity and cervical length will be compared between the groups. The main study endpoints will be sensitivity, specificity, and area under the ROC curve for delivery within 1,2,4,7, and 14 days from the measurement.

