#### EHG signal analysis

All signal processing and analysis will be performed afterwards offline without knowledge of the pregnancy outcome. Identifying the CV vector will consist of three steps: selection of the contraction segments, estimating the time delays between the channels and calculating the CV vector, see Figure 2. The automatic selection of contractions will be based on the estimate of the internal uterine pressure (eIUP) which is derived from the EHG signal [18]. The algorithm used for the eIUP, as well as the algorithm used for detection of onset and duration of contractions, will be adapted to be suitable for the unpredictable nature of premature and non-labor contractions. Prior to the CV analysis, visual review of the signals will be used to optimize the automatic burst selection.

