**Figure 2 F2:**
[figure not shown]
**The method for analyzing the EHG CV.** The EHG is recorded using a fixed configuration of four electrodes plus ground and reference electrodes. The eIUP is derived from the EHG signal and is used for selecting contraction segments. Finally, the delays are estimated in overlapping windows using cross-correlation.

In the signal segments selected as contractions, the CV will be determined in overlapping windows. The length of these windows will be fixed to a value to allow single spikes to be included. Cross-correlation will be used for estimation of the time delay between channels. We will describe the EHG propagation by a CV vector. This CV vector has an amplitude and an incidence angle with respect to the vertical axis. Based on statistical analysis, a threshold value will be determined for the CV vector amplitude. Values above this threshold will be considered to be artefacts and discarded.

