### Study parameters/Endpoints

Patients will be classified as labor group and non-labor group based on the interval between measurement and delivery. The cutoff points will be delivery within 1, 2, 7, and 14 days of the measurement. As primary outcome the EHG parameters will be compared between these groups in terms of amplitude and angle of the CV. In order to be independent of the number of analyzed segments and contractions per patient, the average CV vector will be identified for each analyzed contraction and subsequently the average CV vector for each patient will be determined. As secondary analysis the TVU CL will be compared between the labor and non-labor group. The sensitivity and specificity will be calculated for the EHG parameters and TVU CL for predicting preterm delivery within 1, 2, 7, and 14 days. In order to be independent on arbitrarily chosen cutoff points, the area under the curve of the receiver operating characteristics will be determined.

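### Sensitivity and specificity are main endpoints, but no CV or cervical length cut-off, and no rule for choosing one, is stated; a cut-off picked on the same 100 women would overstate both

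*Protocol article*

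**What the plan says.** Under Statistical analysis the article states: "Using contingency tables, the sensitivity and specificity of the EHG and standard diagnostics will be determined". Study parameters/Endpoints adds the scope: "The sensitivity and specificity will be calculated for the EHG parameters and TVU CL for predicting preterm delivery within 1, 2, 7, and 14 days". The Methods/Design part of the abstract gives these measures their rank: "The main study endpoints will be sensitivity, specificity, and area under the ROC curve". The Discussion again uses them to express diagnostic accuracy.

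Two statements could be mistaken for a diagnostic cut-off, but neither is one:

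- "The cutoff points will be delivery within 1, 2, 7, and 14 days of the measurement" (Study parameters/Endpoints) dichotomises time to delivery. It defines the outcome, not a positive test.
- "Based on statistical analysis, a threshold value will be determined for the CV vector amplitude" (EHG signal analysis, text after Figure 2) concerns a filter. Values above it are discarded as artefacts.

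The article is aware of the cut-off problem in general: "In order to be independent on arbitrarily chosen cutoff points, the area under the curve of the receiver operating characteristics will be determined". It describes no internal or external validation of a cut-off and no correction for choosing one.

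**The concern.** When a cut-off is chosen because it performs well in a sample, and performance is then reported from that sample, chance features of the data are counted as accuracy. Sensitivity and specificity both come out too high on average, and the usual confidence interval from the table does not allow for it. The effect grows as the smaller group shrinks, so windows with few deliveries suffer most.

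Several statements make a cut-off from outside this study hard to import:

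- The Background says earlier CV work in preterm patients relied on visual selection of bursts and spikes.
- EHG signal analysis says the pressure-estimation and contraction-detection algorithms "will be adapted to be suitable for the unpredictable nature of premature and non-labor contractions".
- The artefact threshold is still to be determined.
- The Discussion says the delay estimation differs from the group's previous work.

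No earlier cut-off is cited. The EHG parameters are amplitude and angle, so four windows could mean up to 2 × 4 = 8 EHG cut-offs, with more for cervical length.

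At stake is the accuracy reported for a method that the article wants to bring closer to clinical use.

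**Working it through.** **The plan's own figure.** The only computed figure is 82% power for AUC 0.95 against 0.70 with 7 positive and 11 negative patients (Sample size). It concerns AUCs and says nothing about cut-off bias. With power = Φ((0.25 − 1.96·√V0)/√V1), where V0 and V1 are the variances of the AUC difference under the null and the alternative, uncorrelated tests with V0 = V1 (Hanley-McNeil) give about 40%. A between-test correlation of 0.8 with null variance taken at AUC 0.70 gives 82.3%. The figure is attainable, but only under choices the article does not state. It is not used below.

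**Inputs from the article.** N = 100. About 40% deliver within 7 days, so 0.40 × 100 = 40 positive and 60 negative. Planning AUC for EHG is 0.95. The sample was enlarged to allow for a smaller difference or another allocation ratio, so lower AUCs are fair scenarios.

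**Inputs assumed.** Splits of 20/80 and 10/90 stand for windows with few deliveries, since the article gives no event share for 1, 2 or 14 days. CV is taken as normal with equal variance in both groups.

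**Method.**

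1. The group separation is d = √2·Φ⁻¹(AUC). For AUC 0.95, d = 1.414 × 1.645 = 2.33. The true best cut-off is d/2, with true sensitivity Φ(1.163) = 87.8%.
2. Simulate 6,000 studies per setting and choose the cut-off in each by the stated rule.
3. Optimism = apparent sensitivity in the sample − true sensitivity at that same cut-off, averaged over studies. Specificity is handled in the same way.

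A cut-off fixed in advance has expected optimism of zero.

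**Sensitivity optimism in percentage points, Youden cut-off, N = 100.**

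| Positive/negative | AUC 0.95 | AUC 0.80 | AUC 0.70 | AUC 0.60 |
|---|---|---|---|---|
| 40/60 (7 days) | 3.4 | 4.9 | 5.7 | 6.4 |
| 20/80 (assumed) | 6.1 | 8.7 | 9.8 | – |
| 10/90 (assumed) | 9.9 | 13.6 | 15.3 | – |

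An independent rerun agreed to within about half a point.

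**Specificity optimism, Youden.** At AUC 0.95 it is 2.4 points (40/60), 1.5 (20/80) and 1.0 (10/90). It rises to about 4 points at 40/60 when the AUC is low.

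**Dependence on the rule.** Choosing the point closest to (0,1) at 40/60 gives 2.7 points of sensitivity optimism at AUC 0.95 and 4.0 at AUC 0.70. Choosing the best sensitivity with specificity of at least 90% gives about 1 point or less in every setting.

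**Scale.** With 40 positives and a sensitivity of 0.90, the standard error is √(0.9 × 0.1/40) = 4.7 points. A bias of 3.4 points is then 3.4/4.7 ≈ 0.7 standard errors, always in the favourable direction.

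**The case against.** The strongest reply is that this is a journal article. How a cut-off is chosen, and whether resampling is used, is commonly left to the full protocol or SAP, and its absence here would then be no finding. Much of that stands: the article mentions neither a Youden index nor any other optimisation, and the full protocol may fix a cut-off. What remains is the estimator the article does state, namely table-based sensitivity and specificity in the same women, ranked as main endpoints for a test whose processing is still being adapted. Correcting it changes the reported results; it does more than fill in a detail.

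A second reply is that the plan already protects itself. It adds the AUC to avoid arbitrary cut-offs, the sample size rests on AUC, the primary outcome under Study parameters/Endpoints is the group comparison of CV, and signal processing is blind to outcome. This is correct for the AUC and the comparison, which need no CV cut-off. It does not reach sensitivity and specificity, because blinded processing does not fix where a test is called positive.

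A reader might infer three stronger things that the article does not support:

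- That the plan optimises the cut-off on these data. This is likely, but not stated.
- That sensitivity is inflated by 5 to 15 points throughout. At the planning inputs it is about 3.4 points. At 40/60 it passes 5 only when the AUC is about 0.75 or lower, and the upper range needs event numbers the article does not give.
- That CV would therefore look better than cervical length read at a conventional value. No cervical length cut-off is given either, and both tests are treated in the same sentence. If both were tuned to the data, both would carry optimism.

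**Conclusion.** The point holds in conditional form. Two of the three accuracy measures named as main endpoints depend on a cut-off that the article neither states nor gives a rule for, and nothing described would remove the bias if it were chosen on these women. The size rests on the Youden rule, equal-variance normal CV and N = 100. Only the 40/60 split at 7 days comes from the article; the 10 to 20 deliveries behind the larger figures are assumed. On that basis the overstatement of sensitivity is modest at 7 days and becomes material in sparse windows, with a smaller effect on specificity. It would be close to zero under a fixed-specificity rule and zero in expectation with a cut-off fixed beforehand. That dependence is itself a reason to commit to the rule in advance. The change should be made, but the point does not put the AUC results or the CV group comparison in doubt.

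**What to change.** In Study parameters/Endpoints and Statistical analysis:

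1. Name one rule for setting the cut-off, before outcomes are linked to the EHG results, and use it for CV and cervical length alike.
2. Re-derive the cut-off by that rule in each bootstrap sample or leave-one-out fold, and report optimism-corrected sensitivity and specificity with 95% CI.
3. Do this for every delivery window reported, because the short windows may be the ones with most bias. The list of windows should be settled at the same time: the abstract includes 4 days and the body does not.

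Possible wording: *For each test and each delivery window, the cut-off will be set by [named rule]. The rule will be repeated in every resample, and sensitivity and specificity will be reported after correction for optimism, with 95% confidence intervals.*

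If the full protocol already fixes numerical cut-offs from data outside this study, stating them is enough and no correction is needed.

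The cost is a few sentences, a short resampling loop and slightly less favourable reported accuracy. No data collection changes.
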